| Adverse Reaction (AR)                                 | 
An untoward and unintended response in a participant to a substance, which is related to any dose administered to that participant.
 
A causal relationship between the administered substance and an AE is at least a reasonable possibility, i.e. the relationship cannot be ruled out.
                                                                                                                                                                                                                                                                                                                                                                                                                                                                                                                                                                                                                                                                                                                                                                                                                                                                                                                                                                                                                                                                                                                          |

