| Serious Adverse Reaction (SAR)                        | 
An adverse event that is both serious and, in the opinion of the reporting Investigator, believed with reasonable probability to be due to one of the research treatments, based on the information provided.
                                                                                                                                                                                                                                                                                                                                                                                                                                                                                                                                                                                                                                                                                                                                                                                                                                                                                                                                                                                                                                                                                                                                                                                                           |

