| Suspected Unexpected Serious Adverse Reaction (SUSAR) | 
All SARs would be deemed SUSARs given neither treatment is expected to cause an SAE.
                                                                                                                                                                                                                                                                                                                                                                                                                                                                                                                                                                                                                                                                                                                                                                                                                                                                                                                                                                                                                                                                                                                                                                                                                                                                                                                                    |

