## 2. Reporting procedures for serious adverse events or reactions

Only a serious adverse event (SAE) occurring to a participant will be collected in this study. Reports of related (resulted from administration of any of the research procedures) and unexpected (the type of event is not listed in the protocol as an expected occurrence) SAEs will be reported to the ethics committee and the study steering committee (SSC). For fatal and life-threatening suspected unexpected serious adverse reactions (SUSARs), this will be reported as soon as possible, but no later than 7 calendar days after the PI is first aware of the reaction. Any additional relevant information will be reported within 8 calendar days of the initial report. Non-fatal or non-life-threatening SUSARs will also be reported as soon as possible, and no later than 15 days after the PI is first aware of the reaction.

AEs that are not serious will not be collected, as they offer no scientific value in our case, and have been extensively collected and reported in previous studies of ketogenic diets and are well known. Collecting only SAEs will reduce

the burden to participants such as life-threatening events, incidents resulting in persistent or significant disability/incapacity.

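### The protocol defines an adverse reaction and a serious adverse reaction by different causality tests, so a serious event whose link to the diet cannot be excluded can fall outside the 7- and 15-day reports

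*Combined protocol and SAP*

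**What the plan says.** Protocol Section I.1 (Definitions) treats an event as an adverse reaction when a causal link "is at least a reasonable possibility, i.e. the relationship cannot be ruled out". The serious adverse reaction is not built on that definition. It starts again from the event: "An adverse event that is both serious and, in the opinion of the reporting Investigator", is "believed with reasonable probability to be due to one of the research treatments". For SUSARs, the same section says: "All SARs would be deemed SUSARs given neither treatment is expected to cause an SAE".

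Protocol Section I.2 (Reporting procedures) sends SAEs to the ethics committee and the steering committee under this description: "Reports of related (resulted from administration of any of the research procedures) and unexpected". It then sets the deadlines. Fatal or life-threatening SUSARs are due "no later than 7 calendar days after the PI is first aware of the reaction", and other SUSARs "no later than 15 days after the PI is first aware of the reaction". On collection, the same section says: "Only a serious adverse event (SAE) occurring to a participant will be collected in this study".

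SAP 9 lists SAEs descriptively by type and by their relevance to treatment, with totals by arm. It gives no rule for judging relevance.

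**The concern.** The adverse reaction definition asks whether a link can be excluded. The serious adverse reaction definition asks whether a link is reasonably probable. On a plain reading the second asks for more, and it is the one that controls expedited reporting. A serious event can therefore be an adverse reaction by the protocol's own definition and still not be a serious adverse reaction.

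Two things are at stake. The first is whether the ethics committee and the steering committee hear of such an event within a fixed time. The second is the meaning of the relatedness item in SAP 9, which could be completed under either test. Non-serious events are not collected and Protocol Section L.2 states that there are no early stopping rules, so the handling of individual serious events carries more of the safety oversight than it otherwise would. The primary PHQ-9 analysis is not affected.

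**Working it through.** No arithmetic applies. The check sets the definitions side by side and follows one serious event through them.

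**Inputs**

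- Adverse reaction (Section I.1): a reasonable possibility is enough, explained as a link that has not been excluded.
- Serious adverse reaction (Section I.1): reasonable probability, in the reporting investigator's opinion, with no such explanation.
- SUSAR (Section I.1): all SARs. No separate causality wording, and expectedness removes nothing.
- Related SAE (Section I.2): described by its origin in a research procedure. No degree of certainty and no deadline.
- Deadlines (Section I.2): 7 calendar days or 15 days, for SUSARs only.

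**Steps**

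1. Since every SAR is a SUSAR, the SAR causality test decides whether an event is a SUSAR.
2. Since the deadlines apply only to SUSARs, the same test decides whether a deadline applies.
3. Divide serious events into three groups by the strength of the suspected link to the diet:
   - *Link excluded.* Neither test is met. No deadline under either definition, so no conflict.
   - *Link reasonably probable.* Both tests are met. The event is a SUSAR with a 7- or 15-day limit, so no conflict.
   - *Link not excluded, but not judged reasonably probable.* The adverse reaction test is met. The SAR test, read plainly, is not. The event is not a SUSAR and no deadline applies.
4. Look for another rule that would catch the third group. The general reporting sentence in Section I.2 might, if the event is accepted as related, but it sets no time limit. The steering committee's review of accruing data (Section L.2) has no stated deadline for a single event. SAP 9 governs the final report. None of these gives an expedited limit.

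The conflict is therefore confined to the third group, and for that group the text supplies no deadline.

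**The case against.** Several points on the other side have force.

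- **The wording can be read more gently.** The documents contain no graded scale separating possible from probable, and the SAR definition rests on the investigator's opinion. An investigator who treats the two phrases as equivalent loses nothing. This stands, and it is why the point is that an event *can* miss a deadline. A reader might infer that every possible-but-not-probable event goes unreported; the documents do not support that.
- **The related-SAE wording in Section I.2 need not be a third, higher threshold.** It can be read as saying what the event must be related to, and it covers any research procedure rather than only the treatments. This stands. It is counted here as a further undefined wording, not as a stricter test.
- **Safeguards exist.** All SAEs are collected whatever their cause. Participants are prompted at the weekly call and asked about hospitalisation at week 12 (Section I.1). The steering committee sees accruing data and can take on a safety-monitoring role (Section L.2). Section G.5 lets the investigator stop treatment without a relatedness test. SAP 9 reports all SAEs by arm. This limits the point to timing and classification. A reader might infer that serious harms could go unseen; the documents do not support that.
- **Trial status.** Recruitment had stopped at 88 randomised (SAP 2.2), and the SAP's version history lists version 4.0 as final. A wording change that looks only forward may alter few reports. This affects the remedy rather than the inconsistency.

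A reader might also infer that the protocol demands more certainty as events become more serious. In practice no such gradient operates, because non-serious events are not collected and the lower test is never applied to one.

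**Conclusion.** The inconsistency is real and worth correcting. Two definitions in the same section set different causality tests, and the one that reads as more demanding controls the 7- and 15-day reports. A serious event in which the diet cannot be excluded, but is not judged reasonably probable, can fall outside expedited reporting, and no other rule gives it a deadline.

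The conclusion rests on reading reasonable probability as more than reasonable possibility. If investigators treat them as the same, the practical effect disappears, but a reporting rule should not depend on that.

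The effect is all-or-nothing for each event: a fixed limit or none. Its frequency cannot be estimated. SAP 9 expects SAEs to be very rare, and nothing in the documents shows how many would fall between the two tests. A reader might try to size it as one event over half of the 88 randomised. That would assume both an event and an arm split the readable text does not give; SAP 3.2 bases the safety set on participants who commenced each diet, and SAP 9 plans no related-SAE rate. Capture of SAEs and their totals by arm are unaffected.

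**What to change.** 1. Reconcile the adverse reaction and serious adverse reaction definitions in Protocol Section I.1, and the description of related events in Section I.2, to a single causality standard. One way is to define a SAR as an adverse reaction that is also serious, so that it carries the adverse reaction test. Section I.2 can then say that related is judged by that same test, and keep its reference to research procedures as scope.
2. Apply the chosen standard to SAEs already collected, and make any report that then falls due.
3. State the standard in SAP 9 for the item on relevance to treatment, and in the publication.

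The cost is a short wording amendment, a re-read of the SAEs on file, and possibly a few more expedited reports. No change to the efficacy analysis is needed.

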## 2. Reporting procedures for serious adverse events or reactions

Only a serious adverse event (SAE) occurring to a participant will be collected in this study. Reports of related (resulted from administration of any of the research procedures) and unexpected (the type of event is not listed in the protocol as an expected occurrence) SAEs will be reported to the ethics committee and the study steering committee (SSC). For fatal and life-threatening suspected unexpected serious adverse reactions (SUSARs), this will be reported as soon as possible, but no later than 7 calendar days after the PI is first aware of the reaction. Any additional relevant information will be reported within 8 calendar days of the initial report. Non-fatal or non-life-threatening SUSARs will also be reported as soon as possible, and no later than 15 days after the PI is first aware of the reaction.

AEs that are not serious will not be collected, as they offer no scientific value in our case, and have been extensively collected and reported in previous studies of ketogenic diets and are well known. Collecting only SAEs will reduce

the burden to participants such as life-threatening events, incidents resulting in persistent or significant disability/incapacity.

### 3. Safety of participants

#### 1. What level of baseline safety screening will take place for this research?

If potential participants pass the questionnaires for screening, the researcher will conduct a telephone assessment to assess whether they are on a specific diet before participants can be enrolled, the names and doses of antidepressants, other medical conditions diagnosed by a doctor, and the presence of symptoms of psychosis and suicide risk. Trained RAs will make notes on the semi-structured interview document, recording the main features of the phone call, highlighting areas of particular concern and any other specific details as appropriate. This ensures reliable information is shared and supports accurate safety reporting. The semi-structured interview documentation will be forwarded to the local clinician for their review if there are any reports of suicidal thoughts.

#### 2. Provide details about the safety monitoring of participants and the staff/researchers carrying this out

##### *Safety monitoring*

The team includes two consultant psychiatrists and one of the co-PIs who has received training in suicide assessment and response from the US Department of Veteran Affairs. They will provide training for our RAs with a safety manual that outlines the expectations for the assessments, threshold criteria for contacting 999 or GPs or clinical staff for risk assessment, and common issues that may arise during screening assessment (**APPENDIX 14. SUICIDE ASSESSMENT TRAINING MANUAL**). A link to UK mental health crisis resources will be made available on the study landing page. We will send an automated email to all participants with a link to the resource list at baseline for accessing help should they feel like ending their lives (**APPENDIX 15. Participant Email SMS Scripts**).

The co-PI will facilitate a half-day training for the RAs to review the safety manual, review the assessment measure, and engage in role-plays and supervised practice assessments on how to administer a validated screening interview assessing suicidality. If the role plays are satisfactory, the co-PI will shadow the RA for at least 5 participant screening conversations with potentially eligible participants to assure this process and communication that follows it is done correctly. If the role plays do not meet the required standard, the co-PI will provide additional training for the RAs, review their conversations with participants, and shadow the RA for an additional 3 participant screening conversations until the process and communication is executed correctly.

##### *Suicide or self-harm risk*

PHQ-9 will be completed every 2 weeks and asks participants 'Over the last two weeks, how often have you been bothered by thoughts that you would be better off dead, or of hurting yourself in some way?' with response options 'Not at all, several days, more than half the days, nearly every day.' Participants that report that they have had such thoughts more than half the days or nearly every day will have their risk of suicide assessed by a telephone call using the procedure outlined in Error! Reference source not found.. If the participant screens positive for "high risk of suicide" a triage guideline will be followed if a positive "high risk" of suicidal intent/plan has been indicated. Participants will be notified that they are not currently eligible for the study at this time, and that further evaluation will be required. We will ring 999 if the participant is in crisis. If there is a significant but not imminent danger, we will inform the GP as outlined in our flow diagram. Regular debriefing and reliability meetings with RAs, psychiatrist consultants, and the lead co-PI will take place to discuss this process. If a participant discloses risk of suicide intent or attempt after baseline and is assessed as not imminently at high risk, the participant will be reminded about the crisis resources by the assessor and resent the link of crisis resources (**APPENDIX 7**).

### 3. Give details on the medical cover required and who will provide this cover

We have registered medical doctors in the investigating team who are used to assessing patients with psychiatric disorders. Should suicidal ideation be uncovered or other untoward occurrences, the clinicians will respond appropriately, mostly to ensure that usual medical care is provided by the participant's own GP or mental health crisis team. The trial team will ensure that clinical cover is available each day that data is recorded.

A researcher will contact participants the next working day if the response to the PHQ-9 death and suicide question means this is necessary.

### 4. Will the participants' GP be informed about their participation in the research? In not, please justify

Participants' GPs will receive one letter at baseline after randomisation and another providing a summary of the participant's progress in depression and anxiety severity at 12 weeks. If another letter is needed to make the participant's GP aware of an issue, this will be sent ad-hoc as soon as possible.

We will also inform the participant's GP if potentially serious events occur and the participant is not competent to decide on whether to seek medical assessment.

### 5. What is your planned procedure if an incidental finding is suspected?

In the unlikely event that a person discloses that they have just attempted, or are imminently about to attempt suicide, RAs should attempt to identify the person's current location, if they have not already, and call 999 to alert the emergency services.

If the person mentions they have made specific suicide plans, RAs should ask what the person plans to do, if they know where or when they would do it, whether they have access to what they need to carry out the plan, and if they intend to carry it out. If the person states that they plan to carry this out right now, RAs should identify the person's current location and call 999 to alert the emergency services.

If the person responds that they think of suicide or death very frequently or in some detail, but do not mention any specific plans for suicide, RAs should ask the person to tell them more about what has been going through their mind and follow the relevant line of questioning dependant on the answers given (see Error! Reference source not found.).

Unless the call has ended prematurely due to the person disclosing that they will be attempting suicide, RAs should inform the person that they will be sharing the content of this phone call with a clinical member of the research team.

The RA will contact a clinical member of the research team and relay the details of the conversation with the person, to discuss thoughts disclosed around suicide, and provide details of any actions taken thus far. Emergency contact should be made by telephone and followed up with an email confirming the details of the conversation. However, if the person is known to have ongoing suicidal ideation and the GP or mental health services have a plan as to how to respond to it (e.g. if local services is already supporting the patient for ongoing suicidality and the current report is a continuation of this), then any subsequent communication with the clinician may be by email rather than phone. This is outlined in **APPENDIX 7. FLOW CHART FOR ASSESSING RISK OF SUICIDE** at baseline and after each PHQ-9 questionnaire.

### 6. If an incidental finding has clinical implications, what action will you take?

The assessments concern psychological symptoms, health, and functioning, cortisol, and stool microbiome. There is a risk of the participant declaring suicidal intent and we will follow **Appendix 7. FLOW CHART FOR ASSESSING RISK OF SUICIDE** to deal with this. In the very unlikely event that cortisol concentrations are very low or unusually high, we will inform the participant's GP. No other incidental clinical findings can be revealed by these assessments.

#### 4. Ethical considerations

Research usually carries the risk of some ethical challenge. If this is the case you need to demonstrate your awareness of the problem and your response to mitigate ethical objections.

For guidance on ethical issues, please see <http://researchsupport.admin.ox.ac.uk/governance/ethics/resources>, however the following areas are often a cause for concern:

**1. Will the research involve any participants considered vulnerable in the context of the research (e.g. children, elderly, prisoners, adults at risk)?**

Yes ☐

No ☒

If **yes**, please describe how they are defined as vulnerable and detail any CUREC Approved Procedures or guidance that will be applied to the research (for current documents and templates see <https://researchsupport.admin.ox.ac.uk/governance/ethics/resources>).

During the screening stage we will not enrol participants at risk, such as participants with high suicide risk, psychotic disorders, and other serious physical illnesses.

